**SUMMARY**

This project develops a new form of management of subjects with suspected SAHS and different sleep disorders by applying TIC's. It is the response to the increased detection of patients with SAHS. If there is more cases of suspected SAHS will be more typical cases with problems as well as complex patients that require sleep specialist. Due to the health cost at present these patients must be managed in a cost-effective way. TIC's could be a response. Objectives. 1) Analysis of efficacy and cost effectiveness of two management programs of SAHS. The classic hospital one versus another based on work using ICT. The main variable is the Quebec questionnaire and in cases of CPAP the compliance as the analysis of EuroQol-5D, Epworth, the number side effects, and satisfaction in both groups. Design: Prospective, randomized, controlled, open, parallel in 202 patients (101 per arm). Monitoring will be 6 months and 4 assessments. Statistical analysis: Effectiveness: Changes in the Quebec scale is compared before and after intervention between the two arms using analysis of ANCOVA (premise 2-point improvement in the Telematic group). The other variables, compliance as the analysis of other EuroQol-5D, Epworth were analyzed using independent differences in means (or nonparametric equivalent) or Chi2 for dichotomous variables. Cost-effectiveness: the costs generated by either program will be measured against the effectiveness of the main variables by calculating the ICER following Bayesian techniques

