**Proceedings:**

Sleep studies and CPAP titration. 1) PSG or hospital respiratory polygraph (PR): The technique and analysis will be carried out according to AASM 2012-SEPAR 2011 regulations. 2) PSG or PR home. The technique and analysis will also conform to the aforementioned standardized regulations. The home care nursing group for chronic patients will also deliver the equipment. In this case the data will be transmitted to the hospital via telematics. For CPAP titration the same procedure will be followed except that the company will provide the automatic equipment for titration, the training will be done from the hospital via telematics and if it is a difficult titration will be adjusted for several days according to results observed telematrically. In the usual treatment arm the professionals of the traditional centres will follow the already established processes. Valid studies for PSG or PR will be considered those that comply with the regulations of the Spanish sleep group. As far as treatment is concerned, the SEPAR regulations will be followed (Lloberes et al. 2011).

Follow-up: Patients will be evaluated according to SEPAR general regulations (onset, at 1, 3 months, and 6 months) and above all depending on the medical criteria. Obviously the extra visits made will be valued. The aforementioned questionnaires will be collected and, in the case of CPAP, compliance at the beginning and at the end (CPAP compliance is not collected in the intermediate months because a group is telematic).

**Justification of sample size.** The main study variable is the change in the score of the dimension of the Quebec questionnaire that requires a higher "n". It is estimated that for an alpha error of 0.05, beta of 0.20 and a clinically relevant difference (change in total score ≥2 points on the questionnaire) between the two study groups, a minimum of 101 patients per randomization arm (202 patients in total) is required. An estimated 20% loss (between those who lose and those who do not tolerate CPAP), according to published data on the degree of compliance with CPAP in Spain is estimated at 75-80%.

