**Effectiveness assessment.**

Statistical analysis shall be based on the intention-to-treat principle. The comparison in the changes in the score of the QUEBEC questionnaire (6 months vs. Basal) between both groups will be carried out from the ANCOVA test, obtaining the mean scores at 6 months for each group adjusted by the basal values and other confusing variables such as the BMI, age or the severity of the SAHS. This test will be performed under the assumption of "least squares". Sub-analysis will be performed with the most complex patients in which the same analysis will be replicated. An analysis per protocol will also be carried out in the case of patients with CPAP depending on whether the compliance is less than or not at 4 h/night. For patients without the last follow-up visit, and therefore only with baseline information, the same baseline value will be imputed to the 24-week visit as it is the most conservative option and against the hypothesis of the potential benefit of CPAP intervention. A significant difference of <0.05 will be established for all tests (SPSS version 20 will be used).

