Secondary objectives: Comparison between both arms of the cited questionnaires (Epworth, EuroQol-5D, Satisfaction and number of side effects). In addition to having other variables of interest collected from each patient, these variables may act as covariates that help minimize uncertainty in the estimation of effectiveness and incremental cost. We therefore propose a series of secondary objectives linked to the proposed Bayesian methodology: 1) to develop a cost-effectiveness for more than one measure of effectiveness, also proposing clear decision-making measures that are easy to interpret and 2) to develop a BMA model (Bayesian Model Averaging) for estimating cost-effectiveness. The BMA solution is obtained as an average of the coefficients obtained by all the possible combinations of the covariates weighted by the a posteriori probability of each model. This implies the selection of which variables have predictive capacity since the choice of a single model among all the possible ones does not consider the uncertainty associated with the choice of the correct model. This objective will allow us to innovate this type of study since we will automatically select the relevant variables by means of the Bayesian selection of covariates (17).

Logistics: a) Protocol: based on the present memory; b) Procedure notebook: explains step by step the development of the study and contains all the questionnaires, tests and how to carry them out for standardization, c) Data collection notebook containing the variables to be collected distributed in the visits. The order and form is the same as that of the database; d) Database with domain belonging to the requesting centre.

Ethical aspects: The study will be carried out in accordance with the guidelines and principles of the Declaration of Helsinki and will be approved by the Ethics and Clinical Research Committee. All study subjects will provide informed consent in writing prior to participation. The quality assurance procedure will be permanent (data management, data security procedures are sufficient, effective and well documented).

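### EuroQol-5D and Epworth get unadjusted two-sample tests although their baseline values are collected, which loses precision on these secondary outcomes

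*Protocol*

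**What the plan says.** The Protocol names a test for each group of outcomes in its Summary. The Quebec score is assigned ANCOVA. For the remaining measures the Summary says "EuroQol-5D, Epworth were analyzed using independent differences in means (or nonparametric equivalent) or Chi2 for dichotomous variables".

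Elsewhere in the Protocol:

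- **Variables** lists EuroQol-5D and Epworth next to Quebec as questionnaires to be collected.
- **Proceedings, follow-up paragraph** sets evaluations at onset and at 1, 3 and 6 months, and states "The aforementioned questionnaires will be collected and, in the case of CPAP, compliance at the beginning and at the end".
- **Effectiveness assessment** describes the Quebec model as "obtaining the mean scores at 6 months for each group adjusted by the basal values and other confusing variables", naming BMI, age and SAHS severity as examples. No other scale is mentioned there.
- **Secondary objectives** (the paragraph that follows Cost-effectiveness) lists "Comparison between both arms of the cited questionnaires (Epworth, EuroQol-5D, Satisfaction and number of side effects" without a model. On covariates it adds that "these variables may act as covariates that help minimize uncertainty in the estimation of effectiveness and incremental cost", in connection with the Bayesian cost-effectiveness work.

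**The concern.** Three questionnaires share the same before-and-after structure, yet only one is analysed with its baseline value in the model. The Protocol gives no reason for treating the other two differently. Baseline adjustment costs nothing once the baseline is recorded, and it does two things: it narrows the interval for the treatment difference, and it removes in expectation the effect of a chance baseline gap between the arms.

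Without it, the EuroQol-5D and Epworth comparisons are less informative than the collected data allow. Both scales are also named as secondary effect measures in the cost-effectiveness section, so it matters that their baseline values are handled deliberately there as well.

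**Working it through.** **The plan's own figure.** Proceedings gives a sample size only for Quebec: "for an alpha error of 0.05, beta of 0.20", a difference defined as "change in total score ≥2 points on the questionnaire", and "a minimum of 101 patients per randomization arm (202 patients in total) is required". No SD is stated, so 101 cannot be reproduced; it can only be solved for the SD. Assuming a two-sided test and 101 as the evaluable number, SD = 2 × √(101/2) / (1.960 + 0.842) ≈ 5.07 points. If 101 already contains the 20% loss (80.8 evaluable per arm), the SD is about 4.54. There is no corresponding figure for EuroQol-5D or Epworth, and the variance ratios below depend on neither the SD nor n.

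**Inputs for the check.** 101 per arm comes from the Protocol. The correlation r between baseline and 6 months is my assumption, with a range of 0.3 to 0.7. Equal SDs at both visits are also assumed.

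**Variance of the treatment difference**, relative to unadjusted 6-month means (= 1):

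- change scores: 2(1 − r)
- ANCOVA on own baseline: 1 − r²
- ANCOVA relative to change scores: (1 − r²) / [2(1 − r)] = (1 + r)/2

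| r | Change scores vs 6-month means | ANCOVA vs 6-month means | ANCOVA vs change scores |
|---|---|---|---|
| 0.3 | 1.40 | 0.91 | 0.65 |
| 0.5 | 1.00 | 0.75 | 0.75 |
| 0.7 | 0.60 | 0.51 | 0.85 |

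For every r strictly between 0 and 1, ANCOVA has the smaller variance whichever unadjusted version is intended.

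**In patients and power.** The precision that unadjusted 6-month means reach with 101 per arm would need 101 × (1 − r²), about 92, 76 or 52 per arm, with ANCOVA. The difference detectable with 80% power by unadjusted 6-month means is (1.960 + 0.842) / √(101/2) ≈ 0.39 SD. For that same difference:

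| r | Power, 6-month means | Power, change scores | Power, ANCOVA |
|---|---|---|---|
| 0.3 | 80% | 65.8% | 83.6% |
| 0.5 | 80% | 80.0% | 89.9% |
| 0.7 | 80% | 95.1% | 97.5% |

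**Chance imbalance.** With 101 per arm the baseline difference has a standard error of √(2/101) ≈ 0.14 SD, so 95% of randomisations fall within about ±0.28 SD. Given a baseline gap of 0.2 SD:

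- 6-month means shift by r × 0.2 = 0.06, 0.10 or 0.14 SD at r = 0.3, 0.5, 0.7;
- change scores shift by −(1 − r) × 0.2 = −0.14, −0.10 or −0.06 SD, because subtracting the whole baseline removes more than the gap contributes at 6 months;
- ANCOVA removes the shift in expectation.

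**The case against.** The strongest objection is that nothing planned here is invalid. A two-sample comparison in a randomised trial is unbiased over randomisation and keeps its type I error. The primary outcome is already adjusted, and the Protocol makes no power claim for EuroQol-5D or Epworth. This stands, and it limits the point to efficiency on secondary outcomes and protection against an unlucky allocation.

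A second objection is that the sentence sits in a summary, while the body says only that the arms will be compared; secondary models are often left to an analysis plan. That softens the point but does not remove it. The Summary does name a test, and nothing in the body replaces it.

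Three stronger readings are tempting and are not supported:

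- **That a baseline imbalance is simply left uncorrected.** This is true only if 6-month means are compared. The Summary does not say, and its preceding sentence concerns changes in Quebec, so changes are plausible; the imbalance would then be over-corrected.
- **That the imbalance passes straight into the cost-effectiveness result.** The Protocol describes that analysis separately, as Bayesian modelling with covariates and model averaging. Nowhere is the two-sample result said to feed it. What can be said is that covariates are optional there and that the scale's own baseline is not named.
- **That the whole Quebec covariate set should be copied.** Patients enter on suspicion of SAHS. Under Design, diagnosis follows allocation by arm-specific routes, and usual-care patients may not be referred for a sleep test. Severity therefore appears to be measured after randomisation and may be missing for some.

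The follow-up sentence also speaks of compliance at the beginning. Compliance with CPAP cannot exist before treatment, however, so the argument does not extend to it.

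**Conclusion.** The point holds as a free improvement, not as an error that threatens the trial. The stated tests for EuroQol-5D and Epworth are valid but less precise than ANCOVA on data already planned for collection. Under the assumed r of 0.3 to 0.7, the variance reduction is 9% to 49% against 6-month means and 35% to 15% against change scores.

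The direction is secure for any r between 0 and 1 with equal SDs; the size rests on r, which the Protocol does not give. The figures refer to comparisons of means and do not quantify the loss for the nonparametric alternative that the Summary also permits. A reader might infer a false-positive problem or a distorted cost-effectiveness result, but the document supports neither.

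**What to change.** - State that EuroQol-5D and Epworth at 6 months will be compared by ANCOVA with each scale's own baseline value as covariate.
- Limit any further covariates to those measured before randomisation, for example age and BMI. Leave out SAHS severity found by the sleep test after randomisation.
- Keep two-sample tests for satisfaction, side effects and compliance, which have no pre-treatment value.
- In the Bayesian cost-effectiveness model, always include the scale's own baseline value when EuroQol-5D or Epworth is the effect measure, instead of leaving it to optional covariate use.

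The cost is a few sentences in the Protocol and a check of which covariates are recorded before allocation. No additional visits, data or patients are needed.

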**INTRODUCTION**

This project is aimed at developing a new form of management of subjects suspected of suffering from sleep apneas-hypopneas syndrome (SAHS) and sleep disorders in general. In clinical practice these patients can be divided into 3 large groups: A) Those with a high "pre-test" (with typical signs/symptoms without co-morbidities); B) Patients with suspected SAHS but with significant associated pathology (fibromyalgia, insomnia or other sleep pathology) that may hinder their assessment and require special techniques; and C) Subjects with low pre-test, or special populations (advanced age, pregnancy, stroke, severe heart disease etc.) that are not always easy to guide.

These last two groups frequently consult at different levels of care requiring many tests and their diagnosis is always made in third level units. Group A is easier to care for and it is undoubtedly essential that its management takes place outside the hospitals or at least those of non reference. However, this is not the case for groups B and C. Given that SAHS has penetrated society and among health professionals, there are now a greater number of patients diagnosed from all the groups mentioned. This entails or will entail a series of problems, for example, in the treatment with CPAP of typical patients or high pre-test. In this case, although the proportion of subjects with problems during CPAP treatment (low compliance, local problems, persistence of drowsiness, etc.) will be the same, the total number of patients will be greater.

In addition, as already mentioned, SAHS will coexist with several associated diseases such as severe cardiac pathology or fibromyalgia, or in different populations such as the elderly, pregnant women, children, etc. All these aspects make many patients difficult to manage from a clinical point of view and, consequently, require professionals more specifically prepared to attend to them. With the idea that when a disease is frequent all levels of care must be involved, this project aims to develop a new way of caring for and managing these patients with a high level of quality, adequate compliance and that the procedure is cost-effective. To do this, it is proposed to work through the application of TIC´s, with virtual visits and home studies basically with telemedicine techniques as a thread of care.

This project is the result of the group's own trajectory to diagnose patients with SAHS that began in 1997 with the description of the usefulness of simplified systems. (Parra et al. ERJ 1997, Lloberes et al AJRCCM 1996). Then, using this system for several years in three multicenter studies published by the Spanish sleep group, the previous proposals have been consolidated (Masa et al AJRCCM 2011, Thorax 2011, AJRCCM 2004). We have recently established the usefulness of telemedicine in pilot studies (Isetta et al. EJMR 2013). In this way, and as a result of all previous experience, we believe we are in a position to propose a project aimed at a real transfer in daily practice.

SAHS is very prevalent. It is defined as a picture of symptoms that alter the quality of life together with metabolic, neurological and cardiovascular disorders (1-6) secondary to an abnormal number of episodes of upper airway obstruction. It is associated with traffic accidents (7) and is associated with excess mortality (8). Under-diagnosed patients consume more health resources (9) and it is considered a public health problem of the first magnitude (1). The increase in their knowledge has led to an increase in the demand for consultations and the need for more diagnostic studies; however, in many cases they have not been accompanied by new strategies for diagnosis, treatment and monitoring of the disease. Furthermore, the fact that SAHS is frequently associated with other pathologies result that it is considered a chronic disease (10) that makes it necessary to adopt a new approach to its management in order to make it more viable, cost-effective and, above all, effective. Two points are raised as general concepts to consider:

1. Care levels. As with COPD, and given its prevalence, in SAHS all the health levels must be involved, from family medicine, nurses, general specialists, professionals with expertise in sleep disorders to companies providing respiratory therapies. In other words, networking. Our group has experience in this area, as we started this type of study as early as 2007 we started this type of studies. We showed how general pneumologists (with rotation in sleep during residence) working in non-reference hospitals or in primary centers in connection with the hospital sleep unit, adequately handle many patients with SAHS and especially requesting the corresponding tests in an appropriate way (conventional polysomnography or respiratory - home and hospital - and oximetry) (11,12). This is undoubtedly a very important part of the management of patients with high pre-test.
2. Telemedicine or the application of new information and communication technologies (ICTs) to clinical care. In recent years, medical technology has been widely applied and has been boosted by the incorporation of effective innovations arising from various areas such as bioengineering. One of the few exceptions to this rapid process of application or adaptation to technological advances is found in the medicine of everyday life. Its implementation and penetration in clinical practice is much lower than in other scientific-professional fields or even in our daily lives (13). The health care deficit through telemedicine systems is surprising, especially in sleep pathology, especially in the field of SAHS where new protocols are urgently needed to alleviate its serious health care crisis: under-diagnosis, comorbidity and long waiting lists. Some initiatives have been develop although few, both in the US and in Europe and also in Spain, (14) although very timidly. This project aims to routinely apply TIC´s in the clinical practice of patients with suspected SAHS. A very significant point is the fact that it is necessary to adapt telemedicine to the type of patients, since its application to certain populations may not be effective, quite the opposite. Recently, increased morbidity or even mortality has been described in older multimorbid patients or patients with COPD (Takahashi et al. Arch Intern Medicine 2012, Hallet et al. Ann of Internal Medicine 2012). From our experience in recent pilot studies, patients with suspected SAHS may benefit greatly from ICTs. In order to fully manage the diagnosis, treatment and follow-up procedure in an innovative way (Figure 1), we have carried out a series of pilot studies ranging from training to treatment follow-up, these experiences being very positive, allowing us to face a global process (15).

Currently the majority of patients are followed in the reference centers (Figure 2-A) and obviously in the current context is not logical. Non-complex patients will be managed outside the hospital (Figure 2-B). However, complex cases, such as poor compliance, morbid obesity, surgical treatments, Cheyne Stokes, servoventilation, advanced age or severe associated pathologies, among others, should be treated in sleep units, and it is to be expected that in the future their number may increase significantly (Figure 2-C) and hence that hospital professionals should adapt to this changing reality and develop systems to care for this type of patients, ideally outside the hospital setting to optimize cost effectiveness. ICTs are an option since they allow the use of: a) appropriate diagnostic techniques (out-of-hospital PSG), b) studies of several days as we have recently published -type Holter-) (16) and c) teleconsultations (Figure 1). All of this is managed by sleep specialists (16) as we have verified that it is a very important option as it facilitates consultations that require less time, avoids trips for patients (loss of working hours or their distant residence or their condition prevents them from moving easily). In addition, occasional visits will improve compliance (15).

As a summary, it can be said that in order to settle positively in this difficult and changing situation such as the current one, different strategies of action must be developed. Networking is an option, telemedicine techniques are also an option and the combination of both will probably be the optimal way to arrive at a personalized and cost-effective medicine in which all the care links intervene. Our experience allows us to undertake this broad project that aims to manage the entire process of care to the SAHS in a different way and that fits the reality in part related to what is known as the 4 P's of medicine: 1. Personalized (depends on genome characters) 2. Predictive from individual information that can establish predictions 3. Preventive, from predictions implement preventive measures and 4. Participatory by the patient. For the development of this project, the efficiency and cost-effectiveness will be compared between a traditional system and another that basically uses ICTs (Table 1). In order to do so, two options could be chosen: 1) a study only on the "difficult" population (but in this case the behaviour of the high pre-test group would not be known, which could be very different), or 2) which is the one we have chosen, to study all types of patients, without assessing their initial characteristics. We believe that the latter is better because it will be more real and, above all, that in the subsequent analysis the various groups mentioned will already be analyzed.

